In blunt abdominal trauma, where the spleen is one of the most frequently injured organs, much is known about morbidity and mortality [12]. Internal bleeding caused by abdominal organ injury is one of the main causes of death after trauma, and a missed splenic rupture is the most common cause of preventable death in trauma patients [13,14]. Presently, the standard of care in hemodynamically stable patients is nonoperative management (NOM), involving close observation of the patient, with success rates up to 90% [12]. A recent study among adults with blunt splenic injury suggests that there are prognostic factors for failure of NOM. Strong evidence exists for prognostic patient factors such as age of 40 years or above, Injury Severity Score of at least 25, and American Association for the Surgery of Trauma splenic injury grade of 3 or higher [15]. Failure of therapy leads to more interventions, longer hospital stay, and higher mortality rates, resulting in increased costs and presumably decreased QOL. When NOM fails, angiography and splenic artery embolization (SAE) can be used as a supplement to NOM. The success rate of SAE ranges between 73% and 100%, with an overall success rate of NOM combined with SAE ranging between 86% and 100% (most studies reporting success rates greater than 90%) [16]. Despite this success rate, much remains unknown about splenic function after SAE, although it is speculated that there is a relationship between splenic volume and the immunologic status of the patient [17-20]. Preservation of splenic function might be one of the biggest advantages of NOM and SAE. However, patients treated with SAE have a risk of developing splenic infarction, abscesses, or cysts, with distal embolization having a significantly higher association with major complications compared with proximal embolization [21,22]. Surgery is indicated when a patient is hemodynamically unstable and does not respond to transfusion or when associated intraabdominal injuries require surgical management. Possible disadvantages of surgery are postsplenectomy complications, such as sepsis, thrombocytosis, and a lifetime risk of invasive infections (overwhelming postsplenectomy infection) [23,24]. All complications may have a major impact on patients’ QOL.

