### Sample Size Calculation

As the World Health Organization QOL assessment instrument-Bref (WHOQOL-Bref) comprises multiple facets, the *retrospective data* will be analyzed using a multivariate analysis of covariance (MANCOVA). This technique is more powerful than a univariate analysis of variance, resulting in a required sample size of 135 patients giving a medium effect and power of 0.80. Previous research [26] indicates that the minimal clinically important difference (MCID) of the WHOQOL-Bref slightly varies across its domains. Table 1 shows for each domain the MCID and standard deviation. On the basis of these statistics, the Cohen *d* effect sizes were calculated and transformed via Cohen *f* to the *f*^2^ effect sizes required in the MANCOVA power analysis. It turns out that 138 participants are required to detect the average *f*^2^ of 0.061 with a power of 0.80, given a significance level of .05.

With regard to the *prospective data*, mixed linear modeling will be used. Power analysis is performed for a repeated measures design investigating the interaction between treatment and time. We assumed a significance level of .05 and a medium effect size of partial eta squared of 0.05 and an average correlation of 0.50 among the 5 repeated measurements. On the basis of this, we require 33 participants to test with a power of 0.80, whether the 3 treatment groups differ in their change in QOL over the follow-up time. When assuming an effect size similar to the MCID’s reported in the table above, 27 participants are required to detect the medium effect of *f*=0.248 with a power of 0.80.

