#### Clinical Data

For both the retrospective and prospective study, data will be collected from the electronic patient records and trauma registry (Network Emergency Care Brabant). The trauma registry compiles prehospital and hospital data of all trauma patients admitted after presentation to the emergency department. Patients with splenic injury will be identified by the International Statistical Classification of Disease and Related Health Problems (ICD-10) and Abbreviated Injury Scale (AIS) diagnosis codes starting with S36.x and 5442, respectively.

The collected data concern the following: age, sex, systolic blood pressure, hemoglobin, Glasgow coma scale (at arrival), intubation (Yes/No), imaging (US and/or CT), grading spleen injury (American Association for the Surgery of Trauma; see Table 2)[28], type of treatment (NOM/SAE/splenectomy), complications, hospital stay (days), spleen in situ at discharge (Y/N), reinterventions (Y/N), rehospitalization (Y/N), and mortality.

**Table 2 table2:** American Association for the Surgery of Trauma spleen injury scaling (1994 Revision).

Grade^a^		Injury description
**I**		
	Hematoma	Subcapsular <10% of surface area
	Laceration	Capsular tear <1 cm parenchymal depth
**II**		
	Hematoma	Subcapsular 10%-50% of surface area; or intraparenchymal <5 cm in diameter
	Laceration	1-3 cm parenchymal depth, which does not involve a trabecular vessel

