### Statistical Analysis

All analyses will be conducted using SPSS V24.0 (Statistical Package for Social Sciences, Chicago Illinois, USA). Frequencies and descriptive statistics will be calculated to provide an overview of the characteristics of the study population. Statistical test results will be considered significant at a level of *P*<.05.

Concerning the retrospective study, a MANCOVA will be done after correcting theoretically important covariates to assess the differences between treatment groups on the 4 WHOQOL-Bref domains and the general facet. For each type of treatment, a 1 sample *t* test will be performed for each WHOQOL-Bref scale to compare the QOL scores with reference data.

For both the retrospective and prospective studies, a logistic regression analysis will be performed on the outcome variables’ (1) need for reintervention (yes/no) and (2) for each complication (yes/no), assessing the effect of treatment after correcting for theoretically important covariates. With regard to hospital stay in days, a Kruskal-Wallis test will be performed with the group (type of treatment) and days in hospital. Analysis of covariance will be used to compare proximal versus distal SAE, thereby correcting the effect for theoretically important covariates. To confirm/find prognostic factors for failure of NOM, a logistic regression analysis will be performed if NOM is a failure quickly after treatment. Otherwise, a survival analysis will be performed.

Regarding the prospective study, to assess the differences between groups in their change in QOL over time, a linear mixed model analysis will be conducted. To answer our research question, we will focus on the interaction effect between measurement occasion and treatment group, while correcting for theoretically important covariates. For the repeated measures, an unstructured covariance matrix will be used. Item-level missing values will be imputed according to the guidelines of the questionnaires. Scale-level missing values will be handled directly through maximum likelihood estimation, because the mixed model procedure makes use of all available data for each participant over all time points.

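### One adjusted logistic model of treatment for every complication gives non-finite or unstable contrasts where a complication is impossible or rare in a compared group

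*Protocol article*

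**What the plan says.** The Statistical Analysis section of the protocol article plans, for both cohorts, a logistic regression for reintervention and a further one "for each complication (yes/no), assessing the effect of treatment after correcting for theoretically important covariates". The groups and the outcome come from the Clinical Data section, which records "type of treatment (NOM/SAE/splenectomy), complications, hospital stay (days" and further items, without listing the complications. Specific events are named only in the Background: "patients treated with SAE have a risk of developing splenic infarction, abscesses, or cysts", and for surgery "Possible disadvantages of surgery are postsplenectomy complications, such as sepsis, thrombocytosis, and a lifetime risk of invasive infections". The general significance rule is "Statistical test results will be considered significant at a level of *P*<.05".

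The Sample Size Calculation covers quality of life (QOL) only. For the retrospective cohort it gives "resulting in a required sample size of 135 patients giving a medium effect and power of 0.80" and "138 participants are required to detect the average *f*^2^ of 0.061 with a power of 0.80". For the prospective cohort it gives 33 patients under "a medium effect size of partial eta squared of 0.05 and an average correlation of 0.50 among the 5 repeated measurements", and 27 under f = 0.248. No complication rate and no expected split between treatments is given.

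**The concern.** The same three-group model is prescribed for every complication, with no limit to events that can happen in all three groups. Some of the Background events depend on whether the spleen is present. For those, one cell of the treatment-by-outcome table is empty by construction, and ordinary maximum likelihood cannot estimate the contrast with that group. For uncommon events, a small cohort can produce an empty cell by chance.

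Software usually still prints a coefficient, a standard error and a p-value in this situation, and these carry no information. Complications are among the clinical secondary outcomes, and the authors hope the results will feed a treatment protocol, so such output could be misread as evidence for or against a treatment.

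**Working it through.** **1. The plan's own figures.** These reproduce, so they are usable as reference sizes.
- MANOVA global test (Pillai), 3 groups, 5 outcomes: df1 = 10, df2 = 2(N − 6), λ = 2N·f². With f² = 0.0625 (0.25², taken as the medium effect), N = 135 gives power 0.802. With f² = 0.061, N = 138 gives 0.801.
- Treatment-by-time interaction, 3 groups, 5 occasions, correlation 0.50: df1 = 8, df2 = 4(N − 3), λ = f²·N·5/(1 − 0.5). With f = 0.248, N = 27 gives 0.810. Partial eta squared 0.05 means f² = 0.05/0.95 = 0.0526; the smallest N is then 31 (power 0.807), and 33, the next multiple of three, gives 0.838.

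**2. Empty by construction.** If a group of n patients has no event, its likelihood contribution is (1 − p)^n. This keeps rising as p goes to 0, so the log-odds for that group runs to minus infinity. Neither a larger n nor added covariates restore a finite estimate.

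Unadjusted fits with 46 per group (138/3) and illustrative event counts, in the order NOM/SAE/splenectomy with NOM as reference:
- 0/7/0: the SAE coefficient is 19.9 with SE about 4310. Nothing useful is estimated.
- 3/7/0, the pattern for an event that needs a spleen: SAE versus NOM is ln(7/39) − ln(3/43) = 0.94, with SE √(1/3 + 1/43 + 1/7 + 1/39) = 0.72. That contrast is estimable. The splenectomy coefficient is −18.9 with SE about 4310, a Wald z of about −0.004, although that group had no event at all.

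**3. Empty by chance.** With a common risk r in all groups, P(at least one group has no event) = 1 − Π[1 − (1 − r)^n_g].

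Worked case, N = 33 in groups of 11, r = 0.05: 0.95^11 = 0.569; 1 − 0.569 = 0.431; 0.431³ = 0.080; 1 − 0.080 = 0.920.

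The rates, the splits and N = 300 are assumptions. The 60:20:20 groups are rounded to 20, 7, 7 and to 83, 28, 28.

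| N | Split | r = 2% | 5% | 10% | 20% |
|---|---|---|---|---|---|
| 27 | equal | 0.995 | 0.949 | 0.770 | 0.351 |
| 33 | equal | 0.992 | 0.920 | 0.677 | 0.236 |
| 33 | 60:20:20 | 0.994 | 0.942 | 0.761 | 0.383 |
| 138 | equal | 0.778 | 0.257 | 0.023 | <0.001 |
| 138 | 60:20:20 | 0.848 | 0.427 | 0.102 | 0.004 |
| 300 | equal | 0.347 | 0.018 | <0.001 | <0.001 |

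**4. Events available.** At N = 33, the expected total is 33 × 0.05 = 1.7 events at 5% and 33 × 0.10 = 3.3 at 10%. That is too few for two treatment terms plus covariates, even when no cell is empty.

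**The case against.** A reader might infer that these regressions cannot be estimated at all, or that the named complications each belong to one treatment. The documents do not support that.
- The Background says infarction, abscesses and cysts are risks after SAE. It does not say they cannot follow NOM. For infarction only the splenectomy cell is empty by construction. Sepsis and thrombocytosis are called postsplenectomy complications, but nothing says they are absent after NOM or SAE.
- These events are background examples. The article lists no complications for analysis, and that list may stand in a fuller document.
- Even for postsplenectomy infection, the structural zero depends on how patients are grouped. The article does not say how a patient who starts on NOM or SAE and later loses the spleen is classified.
- The sizes 27, 33 and 138 are QOL requirements. The Study Procedures collect clinical data on all splenic injury patients in the retrospective study and on all eligible patients in the prospective one. The complication analysis may be larger, and chance empty cells then become less likely.
- The Discussion accepts that uncertainty is large for the clinical analysis and already plans propensity score adjustment. That the article names no sparse-data method is not a defect in itself.

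All of this limits the scope. It does not remove the point. More patients do not cure a structural zero, and the Discussion's caveat concerns precision, whereas here the estimate does not exist. The objection is to a method the article does state: an adjusted treatment model for each complication without restriction.

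**Conclusion.** The point holds for particular complications and contrasts. It does not hold for every regression.
- **Impossible events:** where the event cannot occur in one group as that group is defined, the contrast with that group has no finite maximum-likelihood estimate at any sample size. Other contrasts may be sound.
- **Rare events:** in a prospective analysis of about 33 patients in equal groups, at least one empty group is expected with probability about 92% at a 5% risk and 68% at 10%. At 138 patients the figures are 26% and 2%, so the retrospective cohort is exposed mainly for risks of about 5% or less. A 60:20:20 split raises all of these and a larger analysis set lowers them.

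The percentages rest on assumed rates, an assumed split and QOL sample sizes, and should be read as a range. The structural result needs none of these, only a grouping in which the event is impossible for one group. The primary QOL analyses are not affected.

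**What to change.** In the Statistical Analysis section:
1. Limit adjusted treatment models to complications that can occur in every compared group and have enough events, with the minimum number set in advance.
2. Analyse spleen-dependent complications only among patients with a spleen in situ. Status at discharge is already recorded. Because it is observed after treatment, show how many patients this excludes from each treatment group.
3. Fit these models by Firth-penalised logistic regression with few covariates, or use the propensity score already planned.
4. Report the remaining individual complications by treatment as counts with exact confidence intervals and no adjusted test.
5. Optionally, add an any-complication summary defined for all groups, with its components shown because it mixes events of different severity.

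The cost is revised wording, a penalised-likelihood routine beyond the standard logistic procedure, and fewer adjusted tests. No new data are needed.

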### Inclusion and Exclusion Criteria

#### Retrospective Study

The inclusion criteria are patients (1) diagnosed with splenic injury after trauma; (2) who underwent NOM, SAE, or surgery at the ETZ Hospital; (3) diagnosed between January 2005 and February 2017; and (4) who were aged 18 years or older at the time of screening (February 2017). Patients will be excluded from questionnaires in case of (1) insufficient knowledge of the Dutch language (verbal and writing) or (2) obviously, death. Patients treated with SAE will be excluded for magnetic resonance imaging (MRI) when they do not want to or are not able to undergo an MRI abdomen (eg, pregnancy or other contraindications).

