#### Prospective Study

To be eligible to participate, patients (1) must be aged 18 years or older, (2) have splenic injury after abdominal trauma (confirmed by US/FAST and/or CT), and (3) must be treated in 1 of the 10 participating hospitals between March 2017 and December 2018. Exclusion criteria are identical to those of the retrospective study.

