### Study Procedures

#### Retrospective Study

The clinical and imaging data of all splenic injury patients will be collected from the electronic patient files and registered anonymously. To measure QOL, all patients who are still alive will receive a written letter explaining the study, an informed consent form, the questionnaires, and a prestamped return envelope by mail. When a patient is willing to participate, he/she will sign the consent form and send it back in the return envelope, together with the completed questionnaires, assessing QOL and health status. When patients do not complete or return the questionnaires within 2 weeks, they receive a phone call as a reminder. When patients do not want to participate, the reason will be noted if the patient wants to let it be known. The patients who underwent SAE will be called for a voluntary single MRI abdomen at the ETZ Hospital in Tilburg.

This study has been reviewed and approved by the Medical Ethical Committee Brabant (METC Brabant, protocol number: NL54339.028.15) on January 27, 2016. The study has also been approved by the local ethical committee of the ETZ Hospital on February 9, 2016.

**Table 1 table1:** Minimal clinically important difference (MCID) per WHOQOL-Bref domain.

Domain	MCID	SD	Cohen *d*	Cohen *f*	Effect size *f*^2^
Physical	1.545	3.1	0.498	0.249	0.062
Psychological	1.259	2.5	0.504	0.252	0.063
Social	1.274	2.6	0.490	0.245	0.060
Environmental	1.142	2.3	0.497	0.248	0.062
General	0.876	1.8	0.487	0.243	0.059
Average	1.219	2.460	0.495	0.248	0.061

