#### Prospective Study

In each participating hospital, an interventional radiologist and a trauma surgeon will be designated as principal investigators. Each hospital will also have a research assistant, most likely a radiology technologist or a member of the research team. The daily work will be carried out by the research assistant under the supervision of the principal investigator at the ETZ Hospital (CR). The research assistant will check daily whether potential eligible patients were admitted to the hospital. This will be done by checking the subscription list, verbally checking with the attending (resident) radiologist and trauma surgeon, and verifying the data in the electronic patient record. The subscription list will be placed at the dictation station of the radiologist, where the trauma diagnoses are reported. If a patient is treated for a traumatic spleen injury, baseline characteristics will be collected and he/she will be screened for the inclusion and exclusion criteria. The clinical data of all eligible patients will be collected anonymously in the database. As soon as the patient can talk and is lucid, the assistant will visit the patient to provide a verbal and written explanation about the study. The time for consideration of participation is 1 week. When a patient is willing to participate, he/she will sign a consent form. If not, the reason will be noted if the patient wants to let it be known. Each inclusion will be reported to the principal investigator (CR). Total follow-up time is 1 year after treatment with time points at 1 week and 1, 3, 6, and 12 months after treatment.

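### Hospital stay is compared in raw days with no separate treatment of in-hospital deaths, so as written an early death ranks as a short stay

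*Protocol article*

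**What the plan says.** All references are to the protocol article.

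- **The test (Statistical Analysis).** "With regard to hospital stay in days, a Kruskal-Wallis test will be performed with the group (type of treatment) and days in hospital". The variable, the grouping and the test are fixed. No rule is given for a stay that ends in death.
- **Scope of the death exclusion (Inclusion and Exclusion Criteria, Retrospective Study).** "Patients will be excluded from questionnaires in case of (1) insufficient knowledge of the Dutch language (verbal and writing) or (2) obviously, death". For the prospective cohort: "Exclusion criteria are identical to those of the retrospective study".
- **Who is in the clinical data set (Study Procedures).** Retrospective: "The clinical and imaging data of all splenic injury patients will be collected from the electronic patient files and registered anonymously". Prospective: "The clinical data of all eligible patients will be collected anonymously in the database". In the retrospective procedures, only patients still alive are sent questionnaires, so the clinical set is wider than the survivors.
- **What is recorded (Clinical Data).** Hospital stay in days appears in the same list as "reinterventions (Y/N), rehospitalization (Y/N), and mortality".
- **Which patients go to surgery (Background).** "Surgery is indicated when a patient is hemodynamically unstable and does not respond to transfusion". The same sentence adds a second indication: associated abdominal injuries that need an operation.

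**The concern.** A stay in days can end in two opposite ways: discharge alive or death. A rank test on raw days treats them alike, so death on day 1 and discharge on day 1 receive the same rank. The Background reads a short stay as favourable: it mentions a shorter stay when describing embolization as tending to be more cost-effective, and it lists longer stay and higher mortality together as consequences of failed therapy. In this test those two harms would partly cancel.

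If early deaths were spread evenly over the three groups, this would mostly add noise. The Background gives reason to expect otherwise, because haemodynamic instability is one route to surgery. A surgical group with more early deaths would be credited with shorter stay. That could produce a difference where survivors do not differ, or conceal a real excess in survivors' stay. Covariate or propensity adjustment would not cure this, because the fault lies in how the outcome is scored and not in the comparability of the groups.

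**Working it through.** **Step 1. Is there a figure to reproduce?** No. The article states no expected stay, death rate or power for this outcome.

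**Step 2. Do deaths enter the test?** No sentence says so. The places set out above all point that way: the death exclusion is confined to the questionnaires, the clinical data cover all splenic injury or eligible patients, and stay and mortality are recorded on the same patients. Applying the stated test to the stated data set ranks deaths by their days in hospital.

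**Step 3. Direction, by hand.** Suppose stay is equal among survivors and every death precedes every discharge. Let q be the fraction dying in a group and d the fraction dying overall. Deaths then fill the lowest fraction d of the ranks (average d/2), and survivors average (1+d)/2. The group's mean rank, as a fraction of N, is

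q·d/2 + (1−q)·(1+d)/2 = (1 + d − q)/2.

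Take three equal groups with assumed deaths of 2%, 2% and 20% (surgery):

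- d = (0.02 + 0.02 + 0.20)/3 = 0.08
- surgery: (1 + 0.08 − 0.20)/2 = 0.44
- each other group: (1 + 0.08 − 0.02)/2 = 0.53

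A simulation with 46 per group and deaths on days 0-2 gave 0.443 for surgery, against 0.503 with deaths excluded. With survivors' median stay about 10.1 days in every group and 5/10/20/30% surgical deaths, the surgery group's observed median falls to 9.7/9.2/8.1/6.7 days.

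**Step 4. Size, by simulation.** Every input is an assumption except the total of 138. That total is the article's questionnaire sample size for the retrospective study and is used only for scale.

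- Groups: 80 nonoperative, 23 embolization, 35 surgery
- Stay: lognormal, median 8 days, log-SD 0.7
- Deaths: 3% in the two nonsurgical groups
- Test: Kruskal-Wallis at 0.05

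All deaths on days 1-3:

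| Surgical deaths | Equal survivor stay: as written | Survivors only | Surgical survivors stay 50% longer (12 vs 8 days): as written | Survivors only |
|---|---|---|---|---|
| 5% | about 5% | about 5% | about 58% | about 70% |
| 10% | 8% | about 5% | 37% | 68% |
| 20% | 23% | about 5% | 10% | 64% |
| 30% | 51% | about 5% | 8% | 58% |

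20% surgical deaths, with timing spread out:

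| Timing of death | Equal survivor stay: as written | Surgical survivors stay 50% longer: as written | Survivors only |
|---|---|---|---|
| days 1-14 | 5-6% | 38-43% | about 62-65% |
| days 1-21 | about 6% | 55-58% | about 62-65% |

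If the other two groups have 10% deaths instead of 3%, with 20% in surgery on days 1-3, rejection under equal survivor stay is about 9% instead of 23%.

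**Step 5. Reading.** False-positive inflation needs deaths that are early, concentrated in one group and more than a few percent. Loss of power is more general: it is already visible at 5% early deaths and persists when deaths are spread over two weeks.

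**The case against.** The strongest case against has four parts.

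1. **Keeping deaths in is an inference.** A reader might take the article to state that deaths stay in the hospital-stay comparison. It does not. It says whose data are collected, not who is analysed for this outcome, and a fuller protocol or analysis plan could restrict the test to patients discharged alive. This stands as a limit on certainty. It does not remove the point, because the article fixes the test and variable, and the only death exclusion it gives is confined to the questionnaires.

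2. **The direction is conditional.** A reader might infer that the sickest group will look better. The documents do not support that as a fact. They give no number, timing or distribution of deaths, and surgery is also indicated for associated abdominal injuries in patients who need not be unstable. Deaths after a long stay would not act this way. This stands in full.

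3. **The large figures depend on timing.** Rejection of 23% or 51% under equal survivor stay needs every death on days 1-3. Spread over two to three weeks, 20% surgical deaths leave it at about 5-6%. The 138 also describes living questionnaire respondents, not the clinical data set, whose size is not given. Both stand.

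4. **The outcome is secondary, and raw days have a legitimate use.** The Discussion concedes large uncertainty for the clinical results and confounding by indication. Raw bed-days including deaths are also a valid measure of resource use. That lowers the stakes. But the caveats concern precision and comparability, not an outcome that scores a death as a short stay, and the test is listed among the clinical outcomes, where a short stay is read as recovery.

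**Conclusion.** The point holds in a limited form. Followed as written, the analysis ranks an early in-hospital death as a short stay. If such deaths are more common in one treatment group, it is biased toward a shorter stay there or hides a longer stay among that group's survivors. Surgery is the plausible group, not an established one.

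The size cannot be fixed from the documents. Under the assumed inputs it runs from negligible false-positive inflation (5% surgical deaths, or deaths spread over two to three weeks) to rejection of 23% or 51% (20% or 30% surgical deaths, all on days 1-3). Across the less extreme scenarios the main effect is a small to moderate loss of power. It would go too far to say that the plan has a stated rule to keep deaths in, or that the surgical comparison will certainly be misleading. For a secondary outcome this is a cheap improvement worth making, and it does not affect the quality-of-life objective.

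**What to change.** State in the analysis section that:

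- hospital stay is compared between treatments among patients discharged alive;
- in-hospital mortality is reported by treatment beside it;
- one sensitivity analysis is run in which death cannot count as a short stay: either time to discharge alive with death as a competing event, or the same rank test with deaths placed at the worst rank.

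**Cost.** A sentence or two and no new data, since stay and mortality are already collected. Ranking deaths worst needs only a recoding before the planned test.

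**Downside.** The comparison among survivors conditions on an event after treatment, so it cannot stand alone. The worst-rank analysis mixes mortality with stay: with 46 per group, equal survivor stay and 20% early surgical deaths it rejects in about 30% of runs, now against surgery. Reporting mortality alongside lets the reader see which component drives the result.
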